## Abstract

**Background::**

In the last 15 years, large registries and several randomized clinical trials have demonstrated the diagnostic and prognostic value of coronary computed tomography angiography (CCTA). Advances in CT scanner technology and developments of analytic tools now enable accurate quantification of coronary artery disease (CAD), including total coronary plaque volume and low attenuation plaque volume. The primary aim of CONFIRM2, (Quantitative **CO**ro**N**ary CT Angiography Evaluation **F**or Evaluation of Clinical Outcomes: An **I**nte**R**national, **M**ulticenter Registry) is to perform comprehensive quantification of CCTA findings, including coronary, non-coronary cardiac, non-cardiac vascular, non-cardiac findings, and relate them to clinical variables and cardiovascular clinical outcomes.

**Design::**

CONFIRM2 is a multicenter, international observational cohort study designed to evaluate multidimensional associations between quantitative phenotype of cardiovascular disease and future adverse clinical outcomes in subjects undergoing clinically indicated CCTA. The targeted population is heterogenous and includes patients undergoing CCTA for atherosclerotic evaluation, valvular heart disease, congenital heart disease or pre-procedural evaluation. Automated software will be utilized for quantification of coronary plaque, stenosis, vascular morphology and cardiac structures for rapid and reproducible tissue characterization. Up to 30,000 patients will be included from up to 50 international multi-continental clinical CCTA sites and followed for 3–4 years.

**Summary::**

CONFIRM2 is one of the largest CCTA studies to establish the clinical value of a multiparametric approach to quantify the phenotype of cardiovascular disease by CCTA using automated imaging solutions.

## Introduction

1.

Atherosclerosis is the primary cause of coronary heart disease and can remain asymptomatic for many years with an acute coronary syndrome (ACS) or sudden cardiac death often being its first clinical manifestation.^1^ Therefore, coronary artery disease (CAD) is a daunting problem which has spurred a relentless search for the ‘Holy Grail’, namely precise prediction of ACS using non-invasive imaging techniques such as coronary computed tomography angiography (CCTA). The unique characteristics of CCTA enable direct visualization of atherosclerotic plaques and numerous studies showed its strength in excluding “significant” CAD with a near to absolute certainty. Therefore, contemporary global guidelines advocate the use of CCTA in symptomatic patients using ≥ 50% angiographic stenosis (i.e. obstructive CAD) to reflect an increased likelihood of ischemia-causing lesions.^2^ Interestingly, a concise and elegant parameter such as an angiographic stenosis ≥ 50% by CCTA appears also a strong predictor of future major adverse cardiac events (MACE) and mortality.^3^

Much of the multicenter clinical data that supports the prognostic importance of CCTA findings of CAD was generated by CONFIRM, or the **CO**ro**N**ary CT Angiography Evaluation **F**or Evaluation of Clinical Outcomes: An **I**nte**R**national, **M**ulticenter Registry.^4^ The CONFIRM study investigated the incremental prognostic value of CCTA beyond traditional risk factors in 23,854 individuals undergoing CCTA for prediction of MACE and all-cause mortality demonstrating ≥50% stenosis as a strong predictor of future mortality at 2.3 years, and a dose-response relationship to increased risk based upon the number of severe stenoses in coronary arterial distributions.^5^ Furthermore, sex differences were observed, with women developing CAD approximately 10 years later and exhibiting higher risk of mortality than their male counterparts for 2-vessel and 3-vessel/left main disease.^5,6^ Since the initial publications of this study, numerous additional studies have evaluated the prognostic strength of CCTA findings in different subgroups, noting consistently improved risk stratification with CCTA in patients without known CAD, as well as with known CAD, with coronary artery calcium scores = 0, with no treatable CAD risk factors, with diabetes, at age <45 years, with family history of premature CAD, with left ventricular dysfunction, with chronic total occlusions, with chronic kidney disease and post-coronary artery bypass grafting (CABG) and percutaneous coronary intervention (PCI).^5,7–14^

Beyond assessment of stenosis severity, CCTA also enables assessment of coronary atherosclerotic phenotype. Certain plaque features such as positive remodeling, low attenuation plaque, spotty calcifications and the napkin ring sign are the basis of ‘high risk’ plaques which are independent predictors of cardiovascular events and improve risk prediction beyond mere stenosis assessment.^15–19^ Indeed, the landmark SCOT-HEART (Scottish Computed Tomography of the HEART) trial found low attenuation plaque volume quantified from CCTA to provide the most powerful predictive information for future myocardial infarction independent from clinical risk factors, coronary calcium score and stenosis severity.^19^ Despite these great achievements, the prognostic value of a quantitative phenotype of CAD has not been fully exploited. Furthermore, semi-quantitative plaque analyses are time-consuming, require a high level of experience, and are not widely performed. Artificial intelligence (AI) and machine-learning (ML) approaches are increasingly utilized to overcome this barrier, allowing the extraction of quantitative plaque measures such as total plaque volume as well as the volume of plaque subtypes (calcified, partially calcified, non-calcified, fibrous, fibrofatty and low attenuation plaque), length of lesions and numerous other features which may not be visible to the naked eye.^20–22^ CCTA further allows quantification of the whole heart including cardiac chamber sizes, left ventricular mass, or left ventricular scar, all of which have shown clinical and prognostic significance. We will perform combined coronary artery evaluation and cardiac structural evaluation by CCTA, and evaluate the incremental prognostic value.

Therefore, the aim of the CONFIRM2 study is to quantify coronary plaque, stenosis, vascular morphology and cardiac structures to allow for a comprehensive analysis of CCTA images and evaluate multidimensional associations between phenotypic manifestations of cardiovascular disease, demographic and clinical information, and outcomes. We aim to improve risk prediction and provide a platform for precision medicine in patients undergoing CCTA.

## Methods

2.

### Overall study design

2.1.

CONFIRM2 is a multicenter, international, observational cohort study. The clinical implications of CCTA findings including coronary artery disease (e.g., atherosclerosis, stenosis, ischemia, etc), non-coronary cardiac findings (e.g., myocardial, valvular, pericardial, etc), non-cardiac vascular findings (e.g., aortic, pulmonary artery, pulmonary veins, etc), and non-cardiac findings (e.g., emphysema, bone mineral density, etc) will be evaluated. The time-related nature of CCTA will be explored, including cross-sectional (e.g., clinical presentation, baseline laboratory values), time-varying (e.g., changes in clinical presentation, medications and laboratory values over time), longitudinal (e.g., risk prediction for clinical events, treatment effect), and interdependence (e.g., relationship of LA volumes to CAD to epicardial fat) relationships of different CT parameters. Different analytic approaches will include quantitative (e.g., quantitative FDA-cleared software for CCTA analysis), machine learning (e.g., deep learning-based approaches), and radiomics for their value to detect “significant” disease (e.g. hemodynamic significant CAD) and as prognosticator.

### Study objectives

2.2.

#### Primary study objective

2.2.1.

The primary study objective of the CONFIRM2 is to evaluate the prognostic value of quantitative measures of coronary atherosclerotic burden, stenosis, vascular and plaque morphology for prediction of death, myocardial infarction and cerebrovascular events. Machine learning techniques and Cox proportional hazard models will be used to evaluate the selection of the most prognostic value of variables.

#### Secondary objectives

2.2.2.

Secondary objectives include further exploration of the clinical value, prognostic value, and categorization into risk groups of individual atherosclerotic plaque features. Secondary studies will aim to optimize the definition of ‘high-risk plaque features’, determine the associations between whole-heart atherosclerosis evaluation and clinical symptoms, determine the incremental value beyond clinical variables or coronary artery calcium score, evaluate of novel methodologies of the coronary stenosis severity assessment, evaluate prognostic value of vascular morphology (lumen volume, or vessel volume), etc. The time related nature of clinical risk factors, laboratory values or medication usage over time will be evaluated in association with coronary atherosclerotic phenotype. Studies will evaluate associations of plaque with novel antiatherosclerotic medications or serum laboratory markers, and evaluate non common clinical risk factors (menopause, sedentary lifestyle, diet, etc). Associations with myocardial ischemia by several invasive or non-invasive techniques will be evaluated. The clinical value of non-coronary structures such as (peri-coronary) adipose tissue, heart chamber quantification, LV wall characterization, valve assessment will be evaluated for several clinical outcomes, including valve replacement or repair, or other cardiac interventions.

### Study endpoints

2.3.

The primary endpoint of CONFIRM2 is the time to first occurrence of all-cause death.

Secondary endpoints include major adverse cardiac events (MACE), defined by the occurrence of any of the following events:
All-cause death*Myocardial infarction*, defined in accordance to the Universal Definition of Myocardial Infarction as established by the European Society of Cardiology (ESC), American College of Cardiology (ACC), American Heart Association (AHA), and the World Heart Federation.*Cerebrovascular accident*, defined as a neurological deficit lasting ≥24 h or lasting <24 h with a brain imaging study showing infarction.

Tertiary endpoints include:
*Late coronary revascularization*, defined as revascularization ≥90 days following the index diagnostic test.*Valvular intervention*, defined as surgical or transcatheter valve replacement or repair of any cardiac valve.*Congestive heart failure (CHF),* defined by the Framingham Heart Study criteria, and will be made when 2 major criteria are present or 1 major and 2 minor criteria are present concurrently.*Cardiac death*, defined as due to any of the following: 1) myocardial infarction; 2) heart failure (includes death due to CHF, cardiogenic shock or pulmonary edema. All deaths from hypotension (systolic blood pressure <80 mmHg) and/or respiratory failure without other clear etiology should be classified as heart failure; 3) arrhythmic death; 4) unclear cause of death, but cardiac cause cannot be excluded.

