### Targeted population

2.4.

This study will enroll up to 30,000 patients undergoing clinically indicated CCTA and follow-up for 3–4 years. This number is based on empirical data to provide adequate data to permit subgroup analyses such as for sex, ethnicity and cardiovascular risk factor categories in relation to coronary atherosclerosis. Sites participating in the study will be selected based on data quality and quantity of CCTAs per year, and to achieve adequate representation of race and ethnicity. The study is considered non-significant risk because this is an observational registry with no targeted downstream alteration to the clinical care pathway of the patient or additional interventions. CCTA, in both the US (ACC/AHA) and European guidelines (ESC, NICE guidelines), received a class I indication for the use as a first-line test in chest pain patients.^2,23^

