#### Patient eligibility criteria

2.5.1.

Patients referred for clinically indicated CCTA will include those undergoing evaluation for CAD, valvular heart disease or congenital heart disease, and pre-procedural evaluation for CABG, PCI, surgical aortic valve replacement/repair (SAVR), transcatheter aortic valve implantation (TAVI), left atrial appendage (LAA) occlusion, surgical mitral valve replacement/repair (SMVR), transcatheter mitral valve replacement (TMVR), tricuspid valve interventions, patent foramen ovale (PFO) closure, electrophysiological (EP) intervention including pre-pulmonary vein isolation (PVI). All consecutive patients who have presented or are presenting for clinically-indicated CCTA of ≥64-detector rows and who meet all the inclusion criteria and none of the exclusion criteria will be included into CONFIRM2. Further inclusion and exclusion criteria are described in Table 1.

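### MACE as written can include MI and stroke caused by procedures that the scan triggered, which can inflate stenosis associations by an amount the document does not fix

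*Protocol article*

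**What the plan says.** All references are to the protocol article.

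- Section 2.3 (Study endpoints): "The primary endpoint of CONFIRM2 is the time to first occurrence of all-cause death". It then says: "Secondary endpoints include major adverse cardiac events (MACE), defined by the occurrence of any of the following events", and lists all-cause death, MI and cerebrovascular accident (CVA).
- MI is "defined in accordance to the Universal Definition of Myocardial Infarction as established by the European Society of Cardiology (ESC" and other societies. No MI type, procedural exclusion or time window is given.
- CVA is "defined as a neurological deficit lasting ≥24 h or lasting <24 h with a brain imaging study showing infarction". Again there is no limit by cause or time.
- Among the tertiary endpoints, late revascularization is "defined as revascularization ≥90 days following the index diagnostic test". This is the only time window in the endpoint section, and no reason is given for it.
- Section 2.2.1 states the primary objective as the prognostic value of quantitative burden, stenosis and morphology "for prediction of death, myocardial infarction and cerebrovascular events".
- Section 2.4 describes a registry with "no targeted downstream alteration to the clinical care pathway of the patient".
- Section 2.5.1 admits patients scanned for "pre-procedural evaluation for CABG, PCI, surgical aortic valve replacement/repair (SAVR), transcatheter aortic valve implantation (TAVI") and other interventions. Section 2.10 confines the primary analysis to patients evaluated for suspected CAD.
- Section 2.7.2 has an independent committee adjudicate events. Section 2.10 gives a censoring rule for incomplete event data only.

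**The concern.** Stenosis is one of the predictors under test. The Introduction and Discussion describe it as the finding on which current practice mainly turns. Clinicians remain free to act on the scan, so a patient with obstructive stenosis is more likely to have an early PCI or CABG. A stroke during that procedure meets the CVA definition on its wording, and an infarction apparently meets the MI definition. Either is then scored as an event that stenosis predicted.

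The effect is differential. Procedures follow stenosis more closely than they follow plaque composition or vessel morphology, so these events load mainly on stenosis. The study sets out to compare plaque quantification with strategies built on obstructive stenosis, and that comparison on MACE, or on MI and CVA, is what is at stake.

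**Working it through.** **Reading the definitions.** A stroke complicating PCI or CABG is a neurological deficit of the stated duration, or a shorter one with infarction on imaging, so it counts. For MI, inclusion is an inference from adopting the Universal Definition without restriction; its text is not at hand. Revascularization before day 90 is not a late-revascularization endpoint, but nothing in section 2.3 treats a complication of that same early procedure differently from any other event.

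**The plan's own figures.** No event rate, hazard ratio or power is given, so there is nothing to reproduce. What follows is illustration, and every rate is an assumption.

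**Illustration 1: risk ratios per 10,000 suspected-CAD patients.** Assumed: 20% obstructive; 40% of those revascularized early; none of the others revascularized; spontaneous MI/CVA risk 5% with and 2% without obstruction; procedural MI/CVA risk 2% to 5% per procedure.

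- Spontaneous events: 2,000 × 5% = 100 and 8,000 × 2% = 160. Risk ratio = 5% / 2% = 2.5.
- Procedural events: 2,000 × 40% × (2% to 5%) = 16 to 40.
- All MI/CVA: 116/2,000 = 5.8% to 140/2,000 = 7.0%. Risk ratio = 5.8/2 to 7.0/2 = 2.9 to 3.5.
- Procedural share in the obstructive group: 16/116 = 14% to 40/140 = 29%.
- If 2% of the non-obstructive group are also revascularized: 160 × (2% to 5%) = 3.2 to 8 further events, so that group's risk is 2.04% to 2.10%. The ratio becomes 5.8/2.04 = 2.84 to 7.0/2.10 = 3.33.
- Full MACE, adding assumed deaths of 4% and 2% without overlap, and no procedures in the non-obstructive group: 9%/4% = 2.25 without procedural events, and 9.8%/4% = 2.45 to 11%/4% = 2.75 with them. Death dilutes the effect.

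**Illustration 2: hazard ratios over 3.5 years** (follow-up is stated as 3 to 4 years). Apparent HR = ratio of cumulative hazards, where H = rate × 3.5 − ln(1 − revascularized share × procedural risk). Assumed: spontaneous MACE 1% to 2% per year without obstruction; early revascularization 20% to 40% with and 1% to 2% without obstruction; procedural risk 2% to 10%.

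- One case in full, with spontaneous HR 2.0, 1% per year, 40% and 2% revascularized, and 5% procedural risk: H without obstruction = 0.035 + 0.001 = 0.036; H with = 0.070 + 0.0202 = 0.0902; apparent HR = 2.51.
- Over the grid, a spontaneous HR of 1.0 appears as 1.05 to 2.05, and one of 2.0 as 2.05 to 3.00.
- Across spontaneous HRs of 1.0 to 3.0, procedural events are 2% to 54% of MACE in the obstructive group.

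**Opposing effect.** In the worked case, let revascularization also lower later spontaneous hazard by 30% in those treated. Spontaneous hazard with obstruction is 0.070 × (1 − 0.4 × 0.3) = 0.0616. The HR is (0.0616 + 0.0202)/0.036 = 2.27 for all MACE and 0.0616/0.035 = 1.76 for MACE without procedural events. Against 2.00, the errors are +0.27 and −0.24.

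**The case against.** The stated aim is prognostic. Total MI and stroke risk under usual care is a legitimate target, and inflation is an error only if the reader wants the risk carried by the disease itself. The opposing-effect calculation supports this: dropping procedural events does not recover the untreated association, because revascularization also acts on later events. This stands, and it is why the all-inclusive MACE should not be displaced.

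It can also be said that an adjudication charter or SAP, not shown, may already classify events by cause. That is possible. But section 2.3 does state the definitions, and as stated they make no distinction. The tested stenosis measure comes from blinded core-laboratory software rather than from the clinical read that drives treatment; the two will be correlated, so this weakens the path without closing it.

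Three stronger readings are tempting and not supported.

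- A reader might infer that planned CABG, PCI, SAVR or TAVI contaminates the primary analysis. Section 2.10 limits that analysis to suspected CAD.
- A reader might infer that the plan contradicts its own reasoning by giving only revascularization a 90-day window. A wish to leave out test-driven procedures is plausible, but the document gives no reason for the window.
- A reader might infer that the stenosis-MACE association is wholly or mainly produced by acting on the scan. The document supports possible inflation of unknown size, no more.

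**Conclusion.** The point holds within limits. As worded, CVA certainly and MI apparently count whatever their cause, so complications of scan-triggered procedures can enter the outcome that stenosis is said to predict. Counting them pushes the stenosis association upward relative to plaque and morphology. Under the assumed ranges the effect runs from negligible (HR 1.0 seen as 1.05) to large (1.0 seen as 2.05); the document does not say where in that range the study lies.

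The formal primary endpoint is all-cause death, and its definition is not affected by this point. MACE is secondary. The concern still reaches the central question, because the primary objective names MI and cerebrovascular events alongside death; that mismatch between sections 2.2.1 and 2.3 is a separate matter to reconcile. Planned procedures bear only on registry-wide and secondary analyses. This is a worthwhile, inexpensive improvement, not a flaw that invalidates the design.

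**What to change.** In sections 2.3 and 2.7.2, have the adjudication committee mark each MI and CVA as procedure-related or spontaneous. Keep the all-inclusive MACE as defined. Report procedure-related events separately. Pre-specify a companion analysis of MACE without procedure-related MI and CVA, and show it beside the all-inclusive result for every stenosis-versus-plaque comparison.

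The cost is one adjudication field and one extra analysis. The committee already receives ECGs, troponin trends, angiograms, brain imaging, neurology reports and discharge summaries. Recruitment began in 2021, so the longer the flag is delayed, the more events would need re-review. The companion analysis has fewer events: in Illustration 1, with no procedures in the non-obstructive group, 16/276 = 6% to 40/300 = 13% fewer MI/CVA events. It leaves procedure-related deaths in the composite and does not remove the effect of revascularization on later events, and the report should say so.

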#### Patient evaluation

2.7.1.

At baseline, clinical, demographical, laboratory, and imaging data will be collected and entered into the case report form. The indication for CCTA includes: CAD evaluation (symptomatic stable; symptomatic acute; asymptomatic [abnormal stress or other], asymptomatic screening), asymptomatic pre-operative evaluation, TAVI, LAA occlusion, TMVR, tricuspid valve interventions, pulmonary vein ablations, electrophysiological evaluation, congenital heart disease, or other. The following laboratory assessment will be collected: serum creatinine, total cholesterol, LDL-C, HDL-C, triglycerides, HbA1C, CRP, Lp(a), Troponin, BNP. Patient demographics include age, sex, ethnicity/race, height, weight, and vital signs. Patient history of CAD includes prior myocardial Infarction (MI), PCI, and CABG. Concomitant medications will be collected: antiplatelet agents, oral anticoagulants, anti-hypertensives, anti-arrhythmics, Hairt failure medications, lipid lowering agents, diabetic agents, smoking cessation agents, anti-depressants, and pulmonary medications. Risk factors include hypertension, dyslipidemia, diabetes, family history, smoking, sedentary lifestyle, peripheral arterial disease, gestational hypertension, gestational diabetes and menopause. Hypertension was defined as a blood pressure of ≥140/90 mmHg or the use of antihypertensive medication. Dyslipidemia was defined as a total cholesterol level of ≥5 mmol/L or treatment with cholesterol-lowering medication. Patients were classified as having diabetes if they were receiving treatment with oral hypoglycemic drugs or insulin. A positive family history of CAD was defined by the presence of CAD in first-degree relatives younger than 55 years in men or 65 years in women. Imaging data (including actual DICOM images) besides the CCTA will be also collected such as a nuclear myocardial perfusion imaging, CMR stress perfusion imaging, invasive coronary angiography, fractional flow reserve (FFR), optical coherence tomography, and intra vascular ultra sound (IVUS).

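### The tertiary valvular-intervention endpoint counts valve procedures already planned at the index scan, so an unknown and possibly dominant share of its events is fixed at baseline

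*Protocol article*

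**What the plan says.** All references are to the Protocol article.

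- **2.3 Study endpoints (tertiary).** Valvular intervention is "defined as surgical or transcatheter valve replacement or repair of any cardiac valve". Nothing is said about when counting starts or about procedures already scheduled.
- **2.3, same list.** Late coronary revascularization does carry a start rule: it is "defined as revascularization ≥90 days following the index diagnostic test".
- **2.5.1 Patient eligibility criteria.** Enrolment covers "All consecutive patients who have presented or are presenting for clinically-indicated CCTA". The eligible pre-procedural indications include "surgical aortic valve replacement/repair (SAVR), transcatheter aortic valve implantation (TAVI") and "surgical mitral valve replacement/repair (SMVR), transcatheter mitral valve replacement (TMVR), tricuspid valve interventions". Table 1 does not exclude patients with a planned valve procedure.
- **2.2.2 Secondary objectives.** Among the non-coronary measures, "valve assessment will be evaluated for several clinical outcomes, including valve replacement or repair".
- **2.7.1 Patient evaluation.** The CCTA indication is recorded at baseline. The list includes "asymptomatic pre-operative evaluation, TAVI, LAA occlusion, TMVR, tricuspid valve interventions" and ends with a residual category. It does not name SAVR or SMVR.
- **2.10 Statistical methods.** The primary analysis is confined to patients scanned for suspected CAD. No population is stated for the valve endpoint.

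**The concern.** Some patients enter the cohort because a valve procedure is being prepared. When that procedure takes place, the definition in 2.3 scores it as an event. It was not predicted by the scan; it was the reason for the scan.

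This matters because 2.2.2 uses valve replacement or repair as an outcome for valve assessment and heart-chamber measures. Patients in a valve work-up are likely to differ from the rest of the cohort on exactly those measures. A hazard ratio or AUC for this endpoint could look strong because the measure recognises who was referred for a valve procedure, without saying anything about who will come to need one. The revascularization endpoint beside it has some protection through its start rule; the valve endpoint has none.

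**Working it through.** The article gives no event rate, expected count or share of patients by indication for this endpoint, so there is no stated figure to reproduce. The check has two parts.

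**Part 1: does the text count the planned procedure?** Section 2.5.1 admits the patient scanned for valve planning. Table 1 does not remove that patient. Section 2.3 counts any replacement or repair of any valve from the index scan onward. The suspected-CAD restriction in 2.10 applies to the primary analysis only. Read as written, the planned procedure is an event. This step needs no assumed number.

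**Part 2: how large could the planned share be?** From the article: N = 30,000 (the maximum) and follow-up of 3-4 years. The following inputs are assumptions, not figures from the article:

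- f, share of the cohort scanned to plan a valve procedure: 0.5-10%
- p, probability that the planned procedure is done: 0.6-0.8
- b, probability of an unplanned valve intervention during follow-up in everyone else: 0.5-3%

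Formulas:

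- planned events = N × f × p
- incident events = N × (1 − f) × b
- planned share = f·p / [f·p + (1 − f)·b]
- planned events reach half of the total at f = b / (p + b)

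With p = 0.8 and b = 1%:

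| f | planned events | incident events | planned share |
|---|---|---|---|
| 0.5% | 120 | 298 | 29% |
| 1% | 240 | 297 | 45% |
| 2% | 480 | 294 | 62% |
| 5% | 1,200 | 285 | 81% |
| 10% | 2,400 | 270 | 90% |

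Extremes of the assumed ranges:

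- Lowest (f = 0.5%, p = 0.6, b = 3%): 90 planned against 896 incident, a share of 9%.
- Highest (f = 10%, p = 0.8, b = 0.5%): 2,400 planned against 135 incident, a share of 95%.

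Share of valve-planning scans above which planned events are the majority (p = 0.8 to p = 0.6):

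| b | threshold f |
|---|---|
| 0.5% | 0.6-0.8% |
| 1% | 1.2-1.6% |
| 2% | 2.4-3.2% |
| 3% | 3.6-4.8% |

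**Effect on apparent accuracy.** Section 2.10 measures its predictive model by AUC. For a yes/no marker, AUC = 0.5 + (sensitivity − false-positive rate)/2. Take the scan indication itself as the marker, with p = 0.8 and b = 1%:

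- f = 1%: sensitivity = 0.008/0.0179 = 0.447; false-positive rate = 0.002/0.9821 = 0.002; AUC = 0.72.
- f = 5%: sensitivity = 0.040/0.0495 = 0.808; false-positive rate = 0.010/0.9505 = 0.011; AUC = 0.90.

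Under these inputs, knowing only why the patient was scanned already gives an AUC that would pass for good prediction.

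**The case against.** The strongest reply is that an endpoint definition is not an analysis set. Section 2.3 names the type of event; it does not say that every enrolled patient enters every tertiary analysis. The protocol does choose populations by analysis, as 2.10 shows for the primary one, and a SAP or sub-study plan could do the same here. The indication is recorded, so patients scanned for TAVI, TMVR or tricuspid planning can be set aside later. Section 2.2.2 also speaks of clinical value in that sentence, which is wider than prognosis.

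Part of this stands: the problem can be repaired with data that are mostly being collected. But the definition is stated here, and as stated it counts the index procedure. That is a rule fixed badly, not a detail left for later, and no other text in the article corrects it.

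Three stronger readings are tempting and are not supported:

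- **That most valve events are planned.** A reader might infer this from the list of pre-procedural indications. The article gives no case mix and no valve-intervention rate, and the assumed ranges above fall on both sides of one half.
- **That planned surgical cases cannot be identified.** The list in 2.7.1 does not name SAVR or SMVR, but it has a pre-operative and a residual category, and it is an article's summary of the case report form. It does not show that the form lacks such codes.
- **That death before a valve procedure is mishandled.** The Kaplan-Meier and Cox text in 2.10 follows from the primary analysis. Competing risks for a tertiary endpoint are normally left to the SAP, which is not at hand, and a Cox model that censors at death already estimates the cause-specific hazard.

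**Conclusion.** The point holds in limited form. It is certain from the text that a valve procedure planned at the index scan counts as an outcome event. The size is unknown: about 9% to 95% of events under the assumed inputs, with planned events in the majority once valve-planning scans exceed somewhere between 0.6% and 4.8% of the cohort. The upper part of that range would be enough to dominate the endpoint, but only the actual case mix can settle it.

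The consequence is confined to analyses that use this tertiary endpoint, chiefly those relating valve and chamber measures to valve replacement or repair. It should be corrected, but it does not threaten the main results of the study.

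**What to change.** For prognostic analyses, take one of two routes:

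1. Count only valve interventions that were not planned at the index CCTA.
2. Exclude from this endpoint's analyses the patients whose recorded CCTA indication was planning of a valve procedure.

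Under either route, report planned procedures separately. Copying the 90-day rule would not be enough by itself, because a planned procedure may be done later than that. Confirm that the indication field identifies SAVR and SMVR planning, and add those codes if it does not. Doing so early helps, since part of the cohort is included retrospectively and planning status may be hard to recover afterwards.

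The cost is minor endpoint and eCRF wording, and fewer valve events. With N = 30,000, p = 0.8 and b = 1% (assumed), removing planned procedures takes the count from 1,200 + 285 = 1,485 to 285 at f = 5%, and from 240 + 297 = 537 to 297 at f = 1%. The events that remain can be read as prognosis.
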